### Endpoints

#### Primary endpoint

The primary endpoint is defined as the rate of DGE according to the ISGPS definition within 30 days after ppPD. The two study groups (pyloromyotomy vs. no pyloromyotomy) are compared with respect to the primary endpoint.

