### Definition of delayed gastric emptying

For this study, the ISGPS definition of DGE was applied [8]. Grade A DGE was present if the nasogastric tube (NGT) was still in place or reinserted between postoperative days (POD) 4 and 7, or if the patient was unable to tolerate a solid oral diet by POD 7. Patients were found to have grade B DGE if the NGT was still in place or reinserted between POD 8 and POD 14, or if the patient could not tolerate a solid oral diet by POD 14. If the NGT was still in place or reinserted after POD 14, or if the patient could not tolerate a solid diet by POD 21, the DGE was classified as grade C in accordance with the ISGPS definition.

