### Sample size calculation

The sample size calculation is based on the primary endpoint "rate of delayed gastric emptying". A retrospective analysis from all patients who underwent ppPD at our institution between 2015 and 2017 revealed a DGE rate of 40.9% in patients who received intraoperative pyloromyotomy compared to a DGE rate of 66.7% in patients who did not receive pyloromyotomy, a difference in absolute risk of 25.8%. The calculation was carried out according to the method described by Campbell et al. for two-group assessments with binary outcomes [30]. Based on these figures, a sample size of 58 patients per treatment group is required to ensure a power of 80% at a two-sided significance level of 5%. To compensate for potential dropouts that would lead to dilution of the treatment effect, an additional 10% of patients will be recruited and randomised. Thus, 64 patients per group will be enrolled, resulting in a total number of 128 patients.

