### Data analysis plan

Continuous data will be presented as mean ± standard deviation or median with interquartile range, depending on the distribution. Categorical data will be presented as numbers with percentages. Approximately normally distributed continuous variables will be compared using the independent *t*-test. Non-normally distributed continuous variables will be compared using the Mann-Whitney-*U* test. Categorical data including the primary endpoint will be compared using the *χ*^2^ test. Fisher’s exact test will be used for categorical data if the requirements for *χ*^2^ test are not met. A two-sided *P* < 0.05 is considered significant. The primary analysis will be conducted in an intention-to-treat (“as randomised”) population. Discarded randomisations as defined in the randomisation section will be excluded from analysis. A multivariate analyisis of the primary endpoint will be performed which will include risk factors with a potential association with DGE (*P* < 0.15). Quality of life data will be analysed in accordance with the EORTC QLQ-C30 scoring manual [31]. An interim analysis was omitted because a sample size calculation was performed, and the study intervention regularly performed in ppPD at our institution is considered a low harm intervention that was not associated with an increased complication rate in a retrospective analysis. A subgroup analysis is performed for patients without intra-abdominal complications to assess the rate of DGE in this patient population.

Cases with missing data for the primary endpoint data resulting from the inability to assess the primary endpoint will be excluded from the primary endpoint analysis. Possible reasons for not being able to assess the primary endpoint are death of a participant before POD 7, unless the patient was able to tolerate a solid diet at that time (see ISGPS definition of DGE above), and the occurrence of a lymphatic fistula with the need for total parenteral nutrition.

Missing quality of life data will be addressed according to the recommendations of the EORTC scoring manual for quality-of-life questionnaires.

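### Read literally, the non-assessable rule can drop patients who already meet the protocol's DGE definition, which can bias the primary comparison in either direction

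*Protocol article*

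**What the plan says.** All references are to the protocol article.

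- **Primary endpoint:** "The primary endpoint is defined as the rate of DGE according to the ISGPS definition within 30 days after ppPD".
- **Definition of delayed gastric emptying:** Grade A has two alternative limbs. The tube limb reads "Grade A DGE was present if the nasogastric tube (NGT) was still in place or reinserted between postoperative days (POD) 4 and 7". The diet limb follows: "or if the patient was unable to tolerate a solid oral diet by POD 7". Either is sufficient. Grades B and C repeat the two limbs at later days.
- **Data analysis plan, population:** "The primary analysis will be conducted in an intention-to-treat" population, glossed as the patients as randomised.
- **Data analysis plan, missing primary endpoint:** cases with missing data "resulting from the inability to assess the primary endpoint will be excluded from the primary endpoint analysis". Two possible reasons are named. One is "death of a participant before POD 7, unless the patient was able to tolerate a solid diet at that time", with a pointer back to the DGE definition. The other is "the occurrence of a lymphatic fistula with the need for total parenteral nutrition", with no time limit and no exception.

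**The concern.** The definition and the exclusion rule do not fit together. The tube limb can be met from POD 4, three days before the cut-off in the death clause. The death clause nevertheless has one exception only, and it concerns the diet limb in its favourable state. Nothing is said for a patient who has already met the tube limb.

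The fistula clause is wider than its apparent reason. Parenteral nutrition makes diet tolerance hard to judge. It does not erase tube dates, nor a DGE status reached before the fistula.

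Death and fistula both occur after randomisation. The article's Background also links intra-abdominal complications with DGE, so patients removed after complications need not be a random subset. At stake are who enters the primary denominator and whether known events are counted in an analysis described as intention-to-treat.

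**Working it through.** **1. The plan's own figure.** Inputs from Sample size calculation: p1 = 0.409 ("DGE rate of 40.9% in patients who received intraoperative pyloromyotomy"), p2 = 0.667 without it, power 80%, two-sided 5%. With the pooled mean p̄ = 0.538:

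n = [1.96·√(2·0.538·0.462) + 0.8416·√(0.409·0.591 + 0.667·0.333)]² / 0.258² = (1.382 + 0.573)² / 0.0666 = 57.4, so 58 per arm. Then 58 × 1.10 = 63.8, so 64. Both stated figures reproduce, and this point does not affect them.

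**2. The two rules side by side.**

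| Patient | Under the DGE definition | Under the exclusion rule, read literally |
|---|---|---|
| Tube in place on POD 4–5, dies POD 6 | Grade A met | excluded |
| Dies before POD 7 while tolerating solid diet | normally no DGE | kept |
| Dies before POD 4 | tube limb not yet reachable | excluded unless tolerating solid diet |
| Tube limb met, then lymphatic fistula with parenteral nutrition | DGE met | excluded |

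Only the first and last rows are direct conflicts.

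**3. Effect on rates.** If a fraction f of an arm is dropped while DGE-positive, its observed rate falls from p to (p − f)/(1 − f). With the same f in both arms, the difference becomes (p2 − p1)/(1 − f). The article gives no rate for f, so 0–10% is an assumed range.

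- No true effect, common rate 53.8%, equal f of 3–5%: each arm's rate falls by 1.4 to 2.4 points and the difference stays 0. Simulated two-sided type I error (400,000 runs, 64 per arm) is 0.051–0.052, against 0.047 with no exclusions.
- No true effect, 5% dropped from pyloromyotomy and none from control: (0.538 − 0.05)/0.95 = 51.4% v 53.8%, a spurious benefit of 2.4 points. Rejection in favour of pyloromyotomy rises from 2.3% to 4.5%. With 10% v 0% it is 5.1 points and 8.2%. With 0% v 5% it is −2.4 points and 1.3%.
- Planned effect, equal 5%: 25.8/0.95 = 27.2 points, and simulated power goes from 83.6% to 86.1%. With 5% v 0% the difference is 28.9 points; with 0% v 5% it is 24.1.

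**4. Effect on the test.** Uncorrected χ², removing DGE-positive patients from numerator and denominator. The planned counts are 0.409 × 64 ≈ 26 and 0.667 × 64 ≈ 43. The 33/64 v 43/64 table is an assumed borderline result.

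| Removed (pyloromyotomy, control) | Assumed 33/64 v 43/64 | Planned 26/64 v 43/64 |
|---|---|---|
| 0, 0 | 0.072 | 0.0026 |
| 3, 0 | 30/61 v 43/64: 0.041 | 23/61 v 43/64: 0.0010 |
| 3, 3 | 30/61 v 40/61: 0.067 | 23/61 v 40/61: 0.0021 |
| 0, 3 | 33/64 v 40/61: 0.112 | 26/64 v 40/61: 0.0052 |
| 5, 0 | 28/59 v 43/64: 0.027 | 21/59 v 43/64: 0.0005 |
| 0, 5 | 33/64 v 38/59: 0.150 | 26/64 v 38/59: 0.0084 |

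At the planned rates, removing one to five from either arm alone keeps P between 0.0005 and 0.0084.

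**The case against.** The strongest reply is that the rule is conditional. It covers cases with missing endpoint data, names only possible reasons, and points back to the DGE definition. A patient who met the tube limb before dying has a known status, so nothing is missing and the patient stays in. That reading is available. But the text spells out an exception for diet tolerance and none for the tube limb, so two careful analysts could build different denominators. The ambiguity stands.

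It can also be said that the rule is prespecified and disclosed, and that as-randomised describes group assignment rather than completeness. That is fair: leaving out outcomes that truly cannot be determined is an open missing-data choice. It does not cover outcomes that are already determined.

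A reader might infer that the comparison is certainly biased towards pyloromyotomy. The article does not support this. With equal exclusions and no true effect the difference stays at zero, and imbalance could run either way. Patients and endpoint assessors are blinded, and the retrospective analysis is reported as showing no raised complication rate.

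A reader might also take the step from 0.072 to 0.041 as the expected consequence. It needs a borderline result and removals from one arm only, and every removed patient must be DGE-positive.

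Finally, a statistical analysis plan that is not shown may hold sensitivity analyses. Their absence here is not the finding.

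**Conclusion.** The conflict is real and should be fixed before analysis; it is not a fatal flaw. Followed literally, the rule removes established DGE cases while keeping early deaths with a favourable diet status, and so understates an arm's DGE rate whenever such a case occurs. The comparison can be biased in either direction if exclusions differ by arm. If a true effect exists, even equal exclusions exaggerate it, by about 1.4 points at 5% per arm.

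The size rests on an assumed number of exclusions, since the article gives none, and is probably small. It matters for the conclusion only when the result is close to the threshold and the exclusions are lopsided. The early-death conflict is confined to deaths between POD 4 and 6 in patients who had met the tube limb; it would be too strong to treat every excluded early death as a lost DGE event.

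**What to change.** Amend the missing-data paragraph of the Data analysis plan in three ways.

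1. Any DGE status already established under the article's definition before death or lymphatic fistula is retained in the primary analysis. A patient who has met the tube limb counts as DGE whatever follows.
2. Only patients whose status truly cannot be determined are excluded, with numbers and reasons reported by arm.
3. A sensitivity analysis covers all randomised patients, once with non-assessable patients counted as DGE and once as best and worst case by arm. Randomisations discarded under the Randomisation section are a separate matter and are not affected.

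Two further options are better kept to sensitivity analyses. Counting all other early deaths as events would turn the endpoint into DGE or death. Recording fistula patients without the tube criterion as DGE-free would rest on half the definition.

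The cost is analysis wording and possibly slightly less favourable DGE rates. Tube dates are already needed for the endpoint, and the sample size stays at 64 per arm.

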## Discussion

DGE is a common complication after ppPD. Despite numerous efforts to reduce DGE, most surgical modifications have not been associated with improved rates of DGE in prospective randomised controlled trials or meta-analysis. This underscores the difficulty of preventing and treating DGE. Several factors a likely to contribute to the development of DGE. Intraoperative endoluminal pyloromyotomy could reduce the potential impact of pyloric dysregulation or pyloric spasm on the development of DGE after ppPD. To our knowledge, this is the first randomised trial to investigate the impact of intraoperative pyloromyotomy on DGE. Results from a meta-analysis and larger randomised trials investigating the influence of pyloric resection during ppPD question pyloric dysregulation as the main aetiology for DGE [20, 22, 32]. Instead, these findings support a multifactorial aetiology and highlight the incompletely understood mechanisms leading to DGE. In our retrospective analysis, we showed that intraoperative endoluminal pyloromyotomy was associated with a significant reduction in the rate of DGE in both univariate and multivariate analyses [27]. Because retrospective studies are inherently subject to certain limitations such as incomplete documentation, interpretation bias and selection bias, we decided to verify our results with a prospective randomised trial.

As quality of life is essential for every cancer patient, it has understandably become an increasing focus of cancer research in recent years [33]. Therefore, we decided to include quality of life as a secondary endpoint, which will be measured with an established and validated questionnaire. This allows us to additionally analyse a strongly patient-centred endpoint.

The trial is currently recruiting patients and the results will provide additional data on a simple surgical technique that could reduce the incidence of postoperative DGE.

## Trial status

The trial has been registered in the German Clinical Trials Register (DRKS00013503), on 27 December 2017. The full WHO trial registration dataset is available through the WHO ICTRP search portal. The protocol version is 2017-03; 16 October 2017, Recruitment began on 16 February 2018. The expected date for recruitment completion is September 2022.

## Data Availability

After publication of the study results, a fully anonymised data set and the statistical code can be made available upon justified scientific request and after ethical approval has been granted. Depending on the extent of the data use and the planned research, either appropriate credit or co-authorship must be granted to the authors of this study. A sample of the CRF used for this study can be provided upon justified scientific request.

## Abbreviations

DGE: Delayed gastric emptying
EORTC: *European Organisation for Research and Treatment of Cancer*
IPMN: Intraductal papillary mucinous neoplasia
ISGPS: *International Study Group of Pancreatic Surgery*
NGT: Nasogastric tube
POD: Postoperative day
ppPD: Pylorus-preserving pancreaticoduodenectomy
